#### Secondary outcome

Shoulder function scores will be measured by the Constant-Murley Score(CMS), which is the most used tool with good reliability and validity for shoulder function scores [29]. The instrument evaluates shoulder function scores from four different domains (pain, daily activity, active ROM, and strength), among which, pain and daily activity are self-reported sub-scales, and the other two domains involve objective assessment of shoulder ROM and shoulder abduction strength. The total score of the instrument is 100, a higher score indicates a better shoulder function.

For investigating the fear of movement of subjects with musculoskeletal injury, the Tampa Scale of Kinesiophobia is always considered to be a reliable and valid instrument. There have been studies that used the Tampa Scale of Kinesiophobia on fear of movement in BCS [30–32]. The original Tampa Scale of Kinesiophobia with 17 items was developed in 1991 by Miller, et al. [33], one of its revised versions with 13 items that has comparable reliability and validity to the original version will be used in this study [34]. The 13-item TSK is a self-report questionnaire with scored on a 4-point Likert scale ranging from 1 (strongly disagree) to 4 (strongly agree). The total score of scale ranges between 13 and 52; higher scores represent stronger fear-avoidance beliefs. Hu has verified the validity and reliability of the Chinese version of the TSK with Cronbach α of 0.778 and reliability of 0.860 [35].

The Disabilities of Arm, Shoulder, and Hand Questionnaire (DASH) is a widely used 30-item self-reported questionnaire that will be used to measure the function and symptoms of the affected upper limb in this study. This questionnaire has the level of agreement that is rated on a five-point Likert scale, and higher scores indicate heavier problems in arm functioning or symptoms. The questionnaire assesses the problems in daily functioning from the arm, shoulder, or hand troubles (21 items), abnormal symptoms of the arm (5 items), as well as the effects of arm functional problems on social activities, work, sleep, and psychology (4 items).

Visual analog scale (VAS) is a convenient, simple instrument with a numeric rating scale marked from 0 to 10 that enables patients to mark their pain intensity on the line. Numerical values from 0 to 10 represent the pain intensity from no “pain” to “worst pain” correspondingly. In this trial, we assess the pain of participants both in rest and free range-of-motion upper limb exercise.

Grip strength will be measured with a grip strength meter. Before the test, adjust the unit and years in the display panel. The participant will be asked to sit down in a chair and bend her knee to 90°, then holds the grip force meter and slowly pulls the handle as hard as possible. Participants test twice, selecting the highest value as the final record.

Arm circumference will be assessed by a non-stretch tape at styloid and every 10 cm intervals from the ulnar styloid up to 40 cm distally. The difference of more than 2 cm of arm circumference between the limbs at any measurement point will be considered as lymphedema. Incidence of lymphedema is the proportion of participants who develop lymphedema accounts for total participants.

DASH and TSK are not originally registered outcomes but were identified as observing indicators before the study began. It was found the TSK has already been reported in patients with breast cancer by referring to articles. To improve the study purpose, the TSK was added. DASH can assess the disability and function of the upper limbs. Compared with shoulder ROM, CMS, and grip strength, DASH can observe the effects of the intervention on daily activity ability in BCS; thus, it was also added.

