### Outcomes measures

Outcomes will be measured by a trained rater who is blinded to the group allocation at baseline (T0) and at 2 weeks (T1), 4 weeks (T2), and 8 weeks (T3) after the operation. It is necessary to mention that the four time points are not originally registered time points; the reason for the adjustment is as follows. Firstly, the investigation and preliminary experiment were conducted after the originally registered protocol, it was found that the four time points in this protocol are significant points in observing shoulder rehabilitation, compared with originally registered time points, and using these four time points can achieve the aim of measuring shoulder function without increasing workload. Secondly, patients regularly follow up at these time points, which will facilitate the rater of conducting measurement face to face with participants on time. The investigation and preliminary experiment are not within this study, and the change occurred before the study began. Participants’ demographic information and medical history are collected at baseline, and the primary and secondary outcomes are as follows.

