### Data collection and management

The baseline assessment will be complete before the operation. The rater will conduct the second, the third, and the fourth assessment (2 weeks, 4 weeks, and 8 weeks after the operation) at the ward or outpatient where patients will have follow-up visits, facilitating the data collecting. A case report form (CRF) that is identified using participants’ numbers is designed, information of group allocation on it is hidden. The rater is asked to record all information down in CRF truthfully, timely, and accurately. An independent clinical assistant who manages the medical history of participants needs to check the completeness and accuracy of data at each evaluation, to avoid modification, an encrypted phone will be used to take photos of data. We also take effective measures to manage the database. Paper form data will be transcribed in a password-protected computer by two independent data entry personnel using the input review mechanism. The final trial data set will be accessed and analyzed by an independent statistician and primary researcher. The data will be uploaded to the ResMan Raw data sharing platform (IPD sharing platform) of the Chinese Clinical Trial Registry in 6 months upon the completion of the trial. The URL of sharing platform is http://www.medresman.org.cn/login.aspx. The article of this study will be submitted to peer-reviewed journals.

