### Data analysis

Data analysis will be processed by an independent statistician and primary researcher using the SPSS24.0 software. All statistical tests will be double sides; the statistical significance is set at *p* value < .05. Means and standard deviation or median and inter-quartile ranges will be calculated for continuous variables normally distributed and non-normally distributed, respectively. Categorical variables will be described as frequencies (*f*) and percentages (%). Demographics and other baseline values will be analyzed using the independent two-tailed *t*-test, non-parametric Mann-Whitney *U*-test, and chi-square test.

This study will adopt the modified intention-to-treat (mITT) principle. The effects of the intervention on primary and secondary outcomes (excluded arm circumference and incidence of lymphedema) between the groups will be analyzed by generalized estimating equation (GEE) from treatment, time points, and the interaction between group and time. Observed values of those outcomes at four assessments time points will be put into GEE, selecting the auto-correlation matrix and the robust standard error estimation method. Taking outcome index as the response variable, the group, time, and interaction of group and time will be incorporated into the model, in addition, selecting radiotherapy, the dominant hand, and type of surgery as covariates. The model includes the main effect and interaction effect, paired comparison variables will be selected, and the least significant difference (LSD) method will be used to adjust the multiple comparison effect. Arm circumference and incidence of lymphedema will be analyzed at each measurement time point between groups using the independent two-tailed *t*-test and chi-square test. In case of missing data, if missing data is completely random, the sample will not be included in the final data analysis. If missing data is incomplete random missing or non-random missing, multiple interpolations will be used to complete missing values.

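### Lymphedema incidence is counted from the between-limb difference at a visit, with no direction and no reference to the pre-operative difference, and neither swelling outcome is compared with a baseline term

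*Protocol article*

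**What the plan says.** The Secondary outcome section describes the measurement: "Arm circumference will be assessed by a non-stretch tape at styloid and every 10 cm intervals from the ulnar styloid up to 40 cm distally". It then gives the case rule, "The difference of more than 2 cm of arm circumference between the limbs at any measurement point will be considered as lymphedema", and the summary measure, "Incidence of lymphedema is the proportion of participants who develop lymphedema accounts for total participants".

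Outcomes are measured "at baseline (T0) and at 2 weeks (T1), 4 weeks (T2), and 8 weeks (T3) after the operation" (Outcomes measures), and "The baseline assessment will be complete before the operation" (Data collection and management).

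The Data analysis section takes both swelling outcomes out of the generalized estimating equation ("excluded arm circumference and incidence of lymphedema"). It analyses them separately: "Arm circumference and incidence of lymphedema will be analyzed at each measurement time point between groups using the independent two-tailed *t*-test and chi-square test".

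**The concern.** The rule and the name of the outcome do not match. The rule detects asymmetry present at a visit, which is a prevalence. The outcome is called incidence and is meant to capture swelling that arises after surgery. A natural difference between the arms that was there before the operation meets the rule. So does a difference in which the unaffected arm is the larger.

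If such women are counted, the reported rate is too high and any true difference between the arms is diluted. For arm circumference, a test at each visit that ignores the pre-operative value gives up precision that the baseline measurement could supply. In a trial of 70 women that loss is worth avoiding.

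**Working it through.** **1. What the text settles.** Measurement points are read as sites, because the rule directly follows the list of sites: the styloid plus every 10 cm up to 40 cm, which makes five. Any one site can trigger the rule.

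| Question | What the article says |
|---|---|
| Must the affected arm be the larger? | Not required |
| Is the pre-operative difference subtracted? | No |
| Are women already over 2 cm at T0 removed from the denominator? | No, it is total participants |
| Does an exclusion criterion remove pre-existing asymmetry? | No; the arm-related exclusions are disease, fracture, deficit, lymphangitis and injury |
| Does the analysis adjust for baseline or hand dominance? | No; dominant hand is a covariate only in the model from which these outcomes are excluded |
| Should a pre-operative difference be available? | Yes; outcomes are measured at T0, before surgery, and the rule needs both limbs |

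Taken literally, testing at each measurement time point includes T0, so a woman could be classed as an incident case before her operation.

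**2. Size of the misclassification.** The article gives no lymphedema rate and no asymmetry SD, so there is no figure of its own to reproduce. Everything in this step is assumed. Let D be the vector of between-limb differences at five sites in a woman with no swelling, normal with mean 0, common SD s and between-site correlation 0.5, with no separate tape error. The share wrongly counted at one visit is P(max |D| > 2 cm). By simulation:

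| s (cm) | Share counted as cases | Expected number of 70 |
|---|---|---|
| 0.5 | 0.03% | 0.02 |
| 0.6 | 0.4% | 0.3 |
| 0.8 | 5% | 3.6 |
| 1.0 | 17% | 12 |

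If only a larger affected arm counted, the shares would be about half. In a separate run with tape error of SD 0.3 cm added at each visit, a rule based on change from T0 of more than 2 cm counted fewer than 0.01% of unswollen women at every asymmetry SD from 0.5 to 1.25 cm.

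**3. Effect on the comparison.** Let f be the share of unswollen women wrongly counted, equal in both arms. A true rate p is observed as p + (1 − p)f, so the observed difference is (1 − f) times the true one. As an illustration, take assumed true rates of 20% and 5% with 35 women per arm (70/2):

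| f | Observed rates | Difference (points) | Power |
|---|---|---|---|
| 0 | 20.0% v 5.0% | 15.0 | 47% |
| 5% | 24.0% v 9.75% | 14.25 | 35% |
| 10% | 28.0% v 14.5% | 13.5 | 28% |
| 20% | 36.0% v 24.0% | 12.0 | 19% |

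**4. Arm circumference.** Adjusting a follow-up value for its T0 value multiplies the standard error by sqrt(1 − r²), where r is the correlation of the two values within arm. At r = 0.5 this is sqrt(0.75) = 0.87. At r = 0.7 it is sqrt(0.51) = 0.71. Both values of r are assumed.

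**The case against.** The strongest reply is that the word develop already signals new onset, that T0 is measured, and that a condensed article may leave the handling of women over 2 cm at T0 to the analysis plan. This stands as evidence of intent. It does not repair the rule, because the article states the threshold, the comparison, the denominator and the test, and these do not carry out that intent.

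Several stronger readings are tempting, and the objection to each of them stands:

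- *That the error biases the comparison towards one arm.* Allocation is random, follows the baseline assessment, and the rater is blinded. Misclassification from pre-existing asymmetry is equal between arms in expectation. Chance imbalance at 35 per arm is possible but has no direction.
- *That the circumference test is swamped by differences in body size and loses most of its precision.* The article does not say whether the value tested is the arm circumference, the between-limb difference or a change. If it is the difference, body size largely cancels. Nothing in the document supports a high baseline correlation for a difference score, so a large gain cannot be claimed.
- *That a fifth or more of unswollen women are miscounted.* With the larger affected arm alone counted, about 21% needs an SD of 1.0 cm and a side to be operated on that is on average 0.5 cm larger beforehand. The article gives no reason to expect that offset.
- *That a main outcome of the trial is at risk.* Lymphedema is the last secondary outcome listed in the abstract and does not appear in the three stated objectives.

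**Conclusion.** The point holds as a defect in a stated rule, not as missing detail. Followed as written, the definition counts pre-existing asymmetry, in either direction, as incident lymphedema, and neither swelling outcome is compared with a baseline term. The expected consequence is an inflated rate and a diluted contrast, with no systematic advantage to either group.

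The size is uncertain. It is negligible if the asymmetry SD is about 0.5 cm, a few women of 70 at 0.8 cm, and about 12 of 70 at 1.0 cm, all under assumed normality, mean 0 and between-site correlation 0.5. The precision gain for arm circumference likewise rests on an assumed correlation. The primary outcome and the longitudinal model are untouched. The change is worth making because it costs almost nothing, not because the trial's conclusions depend on it.

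**What to change.** - **Incidence of lymphedema.** For the incidence analysis, count a case when the affected-minus-unaffected circumference difference has increased by more than 2 cm from T0 at the same site. Keep the 2 cm rule as written as a sensitivity analysis.
- **Arm circumference.** At each follow-up visit, compare the groups by ANCOVA with the T0 value as covariate, in place of the unadjusted t-test, and state which circumference quantity is analysed.

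The cost is a few sentences and one derived variable, from measurements the protocol already schedules. The one drawback is less direct comparability with studies that use the uncorrected 2 cm rule, and the sensitivity analysis covers that.

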### Data collection and management

The baseline assessment will be complete before the operation. The rater will conduct the second, the third, and the fourth assessment (2 weeks, 4 weeks, and 8 weeks after the operation) at the ward or outpatient where patients will have follow-up visits, facilitating the data collecting. A case report form (CRF) that is identified using participants’ numbers is designed, information of group allocation on it is hidden. The rater is asked to record all information down in CRF truthfully, timely, and accurately. An independent clinical assistant who manages the medical history of participants needs to check the completeness and accuracy of data at each evaluation, to avoid modification, an encrypted phone will be used to take photos of data. We also take effective measures to manage the database. Paper form data will be transcribed in a password-protected computer by two independent data entry personnel using the input review mechanism. The final trial data set will be accessed and analyzed by an independent statistician and primary researcher. The data will be uploaded to the ResMan Raw data sharing platform (IPD sharing platform) of the Chinese Clinical Trial Registry in 6 months upon the completion of the trial. The URL of sharing platform is http://www.medresman.org.cn/login.aspx. The article of this study will be submitted to peer-reviewed journals.

### Trial monitoring and quality control

To assess the fidelity of intervention and improve the quality of the trial, the study will be surveilled and monitored by the Ethical Committee and research center every 4 months; they are independent of the study and have no competing interests. The content surveilled includes the number of eligible participants, data, exercise logs. The primary researcher needs to report the processes and problems of the study and put forward corresponding solutions. An interim analysis is required at the mid-term examination, the primary researcher will submit test summary, CRF, and raw data set to the research center at the final examination.

### Data analysis

Data analysis will be processed by an independent statistician and primary researcher using the SPSS24.0 software. All statistical tests will be double sides; the statistical significance is set at *p* value < .05. Means and standard deviation or median and inter-quartile ranges will be calculated for continuous variables normally distributed and non-normally distributed, respectively. Categorical variables will be described as frequencies (*f*) and percentages (%). Demographics and other baseline values will be analyzed using the independent two-tailed *t*-test, non-parametric Mann-Whitney *U*-test, and chi-square test.

This study will adopt the modified intention-to-treat (mITT) principle. The effects of the intervention on primary and secondary outcomes (excluded arm circumference and incidence of lymphedema) between the groups will be analyzed by generalized estimating equation (GEE) from treatment, time points, and the interaction between group and time. Observed values of those outcomes at four assessments time points will be put into GEE, selecting the auto-correlation matrix and the robust standard error estimation method. Taking outcome index as the response variable, the group, time, and interaction of group and time will be incorporated into the model, in addition, selecting radiotherapy, the dominant hand, and type of surgery as covariates. The model includes the main effect and interaction effect, paired comparison variables will be selected, and the least significant difference (LSD) method will be used to adjust the multiple comparison effect. Arm circumference and incidence of lymphedema will be analyzed at each measurement time point between groups using the independent two-tailed *t*-test and chi-square test. In case of missing data, if missing data is completely random, the sample will not be included in the final data analysis. If missing data is incomplete random missing or non-random missing, multiple interpolations will be used to complete missing values.

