**Methods/design:**

This is a prospective, single-blind, two-arm randomized controlled trial. An estimated 70 participants will be randomly allocated to (1) the MT group or (2) the control group. The participants in the control group receive free range-of-motion upper limb exercise, and participants in the MT group will engage in free range-of-motion upper limb exercise based on MT. The intervention will start on the first day after surgery and be completed at 8 weeks after surgery. The primary outcome in this protocol is shoulder range of motion (ROM), while the Constant-Murley Score (CMS); Disability of the Arm, Shoulder, and Hand Questionnaire (DASH); Tampa Scale of Kinesiophobia (13-item TSK); visual analog scale (VAS); grip strength; arm circumference; and lymphedema are the secondary outcomes. Assessment will be conducted before allocation (baseline) and at 2 weeks, 4 weeks, and 8 weeks after surgery.

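### The pre-operative value is a fourth GEE response rather than a covariate and no deciding contrast is named: a group effect averaged over all visits would be three quarters of the post-operative effect, and precision is lost on the other readings

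*Protocol article*

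**What the plan says.** All citations are to the protocol article.

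- **Responses.** Data analysis: "Observed values of those outcomes at four assessments time points will be put into GEE". Outcomes measures defines the four occasions: "at baseline (T0) and at 2 weeks (T1), 4 weeks (T2), and 8 weeks (T3) after the operation".
- **Timing of T0.** Data collection and management: "The baseline assessment will be complete before the operation". Randomization and blinding places the baseline assessment before group allocation. The abstract says of treatment: "The intervention will start on the first day after surgery and be completed at 8 weeks after surgery".
- **Model.** Data analysis: "the group, time, and interaction of group and time will be incorporated into the model", with further adjustment by "selecting radiotherapy, the dominant hand, and type of surgery as covariates". The baseline value of the outcome is not in that list. Standard errors and working correlation: "selecting the auto-correlation matrix and the robust standard error estimation method".
- **Tests.** The same section lists main effects, the interaction and pairwise comparisons. It does not say which of them is the test of treatment.
- **Arm circumference.** "Arm circumference and incidence of lymphedema will be analyzed at each measurement time point between groups using the independent two-tailed" *t*-test (for lymphedema, a chi-square test), with no baseline term.

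**The concern.** Under randomization the expected group difference at T0 is zero, because nothing has yet been done to either group. Entering T0 as a response has two consequences.

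First, any group effect averaged over the four occasions mixes one known zero with three post-operative differences. It is therefore smaller than the effect the trial wants to measure. Since no term is declared decisive, nothing in the article rules out reporting that average as the treatment effect.

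Second, the baseline is not used as efficiently as it could be. The group-by-time terms compare changes from T0, and the visit-wise comparisons ignore T0. Adjusting for T0 is at least as precise as either, apart from the single degree of freedom it uses.

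Arm circumference raises the same issue on its own. Stable differences between women are likely to make up much of its variance, the pre-operative value is collected, and the planned test does not use it.

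**Working it through.** **The plan's own figure.** The Sample size section gives a total of 30 for d = 1.3799, 95% power and alpha 0.05. A two-sided two-sample *t*-test (noncentral *t*) gives power 0.940 with 14 per arm and 0.954 with 15 per arm, so 30 reproduces. The repeated-measures figure of 58 cannot be recomputed, because its means, SDs and correlations are not given.

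**Step 1: dilution of the averaged main effect.** Let δ1, δ2, δ3 be the true group differences at T1, T2, T3, with 0 at T0.

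(0 + δ1 + δ2 + δ3)/4 = (3/4) × (δ1 + δ2 + δ3)/3

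The factor is 3/4 whatever the time pattern. For example, effects 0, 1/3, 2/3, 1 average 0.50 over four visits and 0.667 over the last three. In a 300-run GEE simulation with a true effect of 0.80 at T1 to T3, the averaged main effect came out at 0.61, the visit-wise contrasts at 0.80 to 0.83, and the interaction contrasts against T0 at 0.80 to 0.82. Only the average is diluted.

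**Step 2: power at week 8, like for like.** Inputs: 70 × 0.8 = 56 women, so 28 per arm (Sample size section); two-sided alpha 0.05 (Data analysis). Assumptions: effect 0.75 SD, equal variances, pre/post correlation r of 0.2 or 0.5, no other covariates. Power comes from the noncentral *t* with noncentrality 0.75/√(2v/28), where v is the variance in SD² units.

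| Week-8 comparison | v | r = 0.2 | r = 0.5 |
|---|---|---|---|
| Unadjusted | 1 | 79% | 79% |
| Change from T0 | 2 − 2r (1.6; 1.0) | 59% | 79% |
| Adjusted for T0 | 1 − r² (0.96; 0.75) | 80% | 89% |

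**Step 3: power for averages over visits.** Same inputs, plus an assumed correlation of 0.6 between post-operative visits and r between T0 and each of them.

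- Mean of T1 to T3, unadjusted: v = (1 + 2 × 0.6)/3 = 0.733; power 90%.
- The same mean adjusted for T0: v = 0.733 − r² = 0.693 or 0.483; power 91% or 98%.
- Group main effect over T0 to T3: effect 0.75 × 0.75 = 0.5625; v = [4 + 2(3 × 0.6 + 3r)]/16 = 0.55 or 0.6625; power 80% or 72%.

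**Step 4: at the planning effect.** With d = 1.3799, 29 per arm, and correlations of 0.2 to 0.8 (autoregressive or exchangeable), power is at least 0.99 for the averaged main effect and at least 0.98 for the 3-df interaction. The week-8 change contrast with 28 per arm has power 0.98 at r = 0.2.

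**Step 5: arm circumference.** Variance of the raw *t*-test relative to ANCOVA is 1/(1 − r²): 5.3 at r = 0.9 and 10.3 at r = 0.95. Both correlations are assumptions.

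**Step 6: size of the robust tests.** Two sets of null simulations of the planned GEE (autoregressive working matrix, sandwich SE, 56 or 70 women) gave type I error of 6.2% to 8.3% for the main effect and the interaction, against a nominal 5%.

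**The case against.** The strongest defence is that baseline as a response with a group-by-time term is a legitimate, unbiased model. The section plans the interaction and pairwise comparisons alongside the main effect, and these estimate the post-operative differences at full size. Naming the decisive term may be left to an analysis plan that is not shown. This stands. A reader might infer that the planned analysis shrinks the treatment effect by a quarter, but the article supports that only if the averaged main effect is the quantity read.

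A reader might also infer a large loss of power by setting the 3-df interaction or the week-8 change score against the adjusted three-visit mean. Those are different targets. Much of that gap comes from degrees of freedom and averaging. Compared like for like at week 8, adjustment gains one point over the unadjusted contrast at r = 0.2 and ten points at r = 0.5. If pre-operative motion predicts post-operative motion only weakly, adjustment buys little. Nor can it be said that the trial loses power it had planned for: the target test behind 58 is not stated, and at the planning effect every reading is well powered. In reply, that effect comes from a study in adhesive capsulitis measured immediately after the intervention, so a smaller true effect here is plausible.

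The unadjusted *t*-test for arm circumference is valid under randomization and concerns a secondary outcome. A five- to tenfold variance penalty should not be read as a property of this trial, because no correlation is given.

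Finally, the unequal gaps between visits might look like an error under an autoregressive working matrix. With robust standard errors they cost efficiency only, and this is not raised as an error.

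**Conclusion.** The point holds in conditional form. The pre-operative value is a fourth response, the baseline outcome is left out of the covariates, and no deciding contrast is named.

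- **If the averaged group main effect is read,** it estimates exactly 3/4 of the mean post-operative effect. This needs only a zero expected difference at T0, which randomization provides.
- **If the interaction or a visit-wise contrast is read,** the estimate is not diluted, but it is less precise than a baseline-adjusted one. The week-8 gain over the unadjusted contrast is small at r = 0.2 and worthwhile at r = 0.5. The gain over change from baseline is larger: 80% against 59%, and 89% against 79%.
- **Arm circumference** is tested validly but with avoidable imprecision, of a size that depends on an unknown correlation.

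The power figures rest on an assumed 0.75 SD effect and assumed correlations. The loss matters only if the true effect is well below the planning value. This is an improvement the trial should make, not a flaw that invalidates the analysis. The modestly liberal robust tests are a secondary matter.

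**What to change.** 1. Use T1, T2 and T3 as responses, with the T0 value of the same outcome as covariate, plus group, visit, group-by-visit and the covariates already planned. Equivalently in purpose, keep T0 as a response but constrain the groups to a common mean there.
2. Name the post-operative contrast that will be read as the treatment effect, for example the group difference at week 8.
3. Analyse arm circumference by ANCOVA on its pre-operative value at each visit, or by the model in item 1.
4. Secondary: fit item 1 as a linear mixed model with Satterthwaite degrees of freedom, or apply a small-sample correction to the robust standard errors. Changing the mean model within GEE does not by itself correct the standard errors.

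The baseline is already collected, so the cost is analysis wording and syntax, with no new data or visits. The change should be fixed and dated before anyone analyses outcomes by group.
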